**8.4** **Subgroup analyses**

Sub-group (or moderator analyses) according to expectations, age, ethnicity, digital literacy and sex will be conducted to examine possible differences in intervention and health outcomes. Data will be analysed using IBM SPSS Software, generating descriptive and inferential statistics with reported effect size, if data availability/quality allows.

**8.5 Participant population**

Any participant who participated in the project will be subjected to statistical or thematic analyses, except for participants who withdraw from the project before data gets anonymized. This date will be explicitly mentioned in the Participant Information and will be two weeks after data collection took place. Moreover, participants who did not opt-in for their platform usage data to be shared with CU lead researchers upon referral to the platform through Diabetes UK will not be subject to statistical analyses and labelled as missing data.

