# 7 TRIAL PROCEDURES

Diabetes UK will refer potential participants through the Diabetes UK website to the platform where they can sign up, giving consent to platform terms and conditions as they sign in to use the Wisk platform whether or not they want to participate in the research (choosing not to participate in the research will not stop them from using the platform). They are also asked to give permission to share their email address and Mixpanel data to be passed on to the lead CU researchers allowing them to contact participants as part of the wider research project. It must be noted that when participants only want their email address to be shared and not their platform usage data they will still be able to participate into the research by filling in the two surveys as Mixpanel data would be labelled as missing at that point. The plaform developers will send email addresses of new users to lead CU researchers in a shared OneDrive folder with weekly updates. Mixpanel data, with email address as an identifying variable for each user, will be shared in a shared OneDrive folder on a weekly basis.

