8.3.2 Primary outcome analysis

Participants will be analysed on health outcomes before and after they used the platform to see if there is an improvement within this group over time. These data will be analysed using IBM SPSS software (version 26) generating descriptive and inferential statistics with reported effect size (if data availability/quality allows). Descriptive data of platform usage (e.g. session frequency, session duration, pages visited, health score for recipes used) will also be provided by the platform developer through Mix panel. These data will be exported into IBM SPSS software (version 26) and will be used to select participants with different engagement levels (low vs. high) for participation in case studies and semi-structured interviews. Where possible descriptive data of platform usage will be related to health outcomes. Results of the case study interviews and semi-structured interviews will be transcribed verbatim and thematically analysed (based on Grounded Theory) resulting in overall key themes. Survey results will be exported to and coded using IBM SPSS software (version 26) and described using descriptive statistics (e.g. frequencies, percentages, medians and means) according to sociodemographic characteristics (e.g. ethnic group, age, digital literacy, educational level, diagnosis and sex).

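### Read literally, section 8.5 drops people who do not share usage data from all statistical analyses, whereas section 7 has them complete both surveys with only Mixpanel data missing

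*Combined protocol and SAP*

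**What the plan says.** Section 7 separates two permissions, email address and usage data. For the case "when participants only want their email address to be shared and not their platform usage data", it says "they will still be able to participate into the research by filling in the two surveys as Mixpanel data would be labelled as missing". Only the Mixpanel variables are treated as missing.

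Section 8.5 defines who is analysed. It opens with a general rule: "Any participant who participated in the project will be subjected to statistical or thematic analyses, except for participants who withdraw" before their data are anonymised. It then adds a further group, "participants who did not opt-in for their platform usage data to be shared with CU lead researchers", and says that they "will not be subject to statistical analyses and labelled as missing data".

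Section 8.3.2 (Primary outcome analysis) states the main comparison: "Participants will be analysed on health outcomes before and after they used the platform". Usage enters that section's health analysis only as an addition: "Where possible descriptive data of platform usage will be related to health outcomes".

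**The concern.** Sections 7 and 8.5 give different rules for one group of people. The grammatical subject of the last sentence of section 8.5 is the participants, not their Mixpanel data, and nothing limits the sentence to usage analyses. Section 8.5 is the only definition of the analysis population in the plan, so an analyst who followed it to the letter would remove these people from everything quantitative, including the before/after comparison of health outcomes.

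Two things would be at stake. First, complete survey pairs would be discarded from an analysis that does not use the missing data source. Second, inclusion in that analysis would depend on a choice made by the participant. The subgroup analyses in section 8.4 would be restricted in the same way. Non-sharers would also have been invited to complete two surveys that are then left out of the statistics.

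**Working it through.** **Step 1: the two rules side by side.**

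| | Section 7 | Section 8.5, last sentence |
| --- | --- | --- |
| Group | Email shared, usage data not shared | Usage data not shared |
| Surveys | Both may be completed | Not mentioned |
| What is missing | Mixpanel data | The participant, as the sentence is built |
| Scope of exclusion | Usage variables only | Statistical analyses, without limit |

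Section 7 does not say in so many words that these surveys are analysed. That follows from inviting the people to take part by survey, and from the general rule that opens section 8.5.

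**Step 2: does another section settle it?** Section 8.6, whose title covers missing and spurious data, deals only with interview recordings and withdrawal. It does not.

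**Step 3: does the before/after analysis need Mixpanel data?** General health, weight, waist, HbA1c, blood pressure, smoking and healthy eating are all asked in both the first survey (Attachment 4) and the second (Attachment 6). None comes from Mixpanel. Mixpanel is needed for the usage outcomes in section 3.2 and for relating usage to health in section 8.3.2. Non-sharers are necessarily missing from those two.

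**Step 4: size, for illustration only.** There is no figure in the plan to reproduce. Section 8.1 gives an anticipated 200 to 300 and says that it was not derived statistically, and no opt-out rate appears anywhere. Assume that N complete pairs include non-sharers, and that a share q of them did not share usage data.

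- Pairs left under section 8.5 = N × (1 − q)
- Relative widening of a confidence interval = 1/√(1 − q) − 1

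| Assumed q | N = 200 | N = 300 | Widening |
| --- | --- | --- | --- |
| 20% | 160 | 240 | 1/√0.8 − 1 = 11.8% |
| 40% | 120 | 180 | 1/√0.6 − 1 = 29.1% |

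The widening depends only on q, not on N, and takes the standard deviation of change to be the same in both groups.

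**Step 5: bias.** The opt-in-only mean change differs from the all-respondent mean change by q × (mean change in sharers − mean change in non-sharers). With q of 20% to 40% and an assumed difference of 0.1 to 0.3 SD, this runs from 0.2 × 0.1 = 0.02 SD to 0.4 × 0.3 = 0.12 SD. If the groups do not differ, it is zero. The documents supply neither term.

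**The case against.** The strongest reply is that this is a drafting slip. Section 8.5 ends by labelling something as missing, and section 7 uses nearly the same expression for Mixpanel data. Data fields are usually labelled missing, and people are not. The authors may well have meant only that usage data are absent for these participants. That is plausible, so the documents do not support the inference that the plan deliberately removes non-sharers. It does not rescue the sentence, which then fails to say what was meant.

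Sections 7.1.1 and 7.2 describe email and Mixpanel sharing together, as if they were one permission. If so, people who declined could not be invited, would have no survey data, and nothing would be lost. Section 7 explicitly separates the two, so the conflict stands, but these sections need aligning as well.

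Some stronger readings should be set aside:

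- A reader might infer that section 8.5 contradicts its own opening sentence. The last sentence adds a second exception to a general rule. The conflict is with section 7.
- A reader might regard Mixpanel as irrelevant to the evaluation. It is not: usage is the second primary outcome category in section 3.2. The point is only that the before/after health analysis can be done without it.
- A reader might infer that the exclusion biases the results in a known direction, for instance through digital literacy. Nothing in the documents shows that non-sharers differ in any characteristic or in outcome change.
- A reader might treat 200 to 300 as complete pairs that include non-sharers. The Project Summary gives that range for data from surveys and Mixpanel together, and section 8.2 says nonresponse has to be allowed for.

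The project is also exploratory: it has no formal hypotheses, and inferential statistics are planned only where possible. That limits the consequences, but it is no reason to leave two rules for who is analysed.

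**Conclusion.** The conflict is real and is in the current text. As written, the last sentence of section 8.5 excludes from statistical analyses the people whom section 7 keeps in the research through both surveys. Following it would discard usable pairs with no gain to the before/after health analysis, and would make inclusion depend on the sharing choice. The loss of precision is certain if any non-sharer completes both surveys. Its size is unknown: the 12% to 29% widening rests entirely on an assumed opt-out of 20% to 40%. Whether there is any bias, and in which direction, cannot be determined from the documents. The conclusion also relies on section 7 being right that the two permissions are separate.

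**What to change.** Replace the last sentence of section 8.5 with:

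> Participants who did not share platform usage data are included in all survey-based before/after and subgroup analyses; they are missing only for Mixpanel outcomes and for analyses relating Mixpanel usage to health outcomes.

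In the same edit:

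- Align the permission wording in sections 7.1.1 and 7.2 with section 7, so that email and usage data are consistently two separate choices.
- Report the number of participants and their baseline characteristics by sharing status.
- Report the self-reported frequency of use from the second survey as a separate measure, not as a substitute for Mixpanel data. Section 7.5.4 itself notes that reported and tracked use may differ, and the item is a five-level category.

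The cost is one sentence in section 8.5, small wording changes in two other sections and one descriptive table. No new data are needed. The change should be made before the data are analysed.

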**8.6 Procedure(s) to account for missing or spurious data**

The semi-structured interviews and case studies will be video and audio recorded. Participants will be informed that they may withdraw any time up until the point that their data is anonymised for analysis. At this point the researchers will not be able to identify their data for withdrawal. This date will be two weeks after the semi-structured interview / case study has taken place and will be mentioned in the Participant Information.

# 9 DATA MANAGEMENT

# 9.1 Data collection tools and source document identification

Diabetes UK will refer potential participants through the Diabetes UK website to the platform where they can sign up allowing CU researchers them to contact participants as part of the wider research project. The case studies and semi-structured interviews will be performed online through the Microsoft Teams application, supporting screen sharing as well as recording while using a Dictaphone for back-up recording. Data files will be automatically saved in Microsoft Streams and files recorded through the dictaphone will be stored immediately after the interview in a dedicated OneDrive folder so the recording can be deleted from dictaphone. Survey data (incl. informed consent) will be collected online through Qualtrics, hosted by CU and will be retained in shared OneDrive which only the project team has access to. CU is responsible to keep records of all participants, all electronically signed ICFs in a shared OneDrive folder that is only accessible by the project team at CU. Disposal date of these data is 3 years from project start.

## **9.2 Data handling and record keeping**

As required by the GCP guidelines CU will ensure that a validated system is used, an audit trial of data changes is maintained ensuring that there is no deletion of entered data, a security system is maintained to protect against unauthorized access, a list of the individuals authorized to make data changes is maintained, adequate backup of the data is maintained and archiving of any source data (i.e. hard copy and electronic) is adequately performed. As such, it will always be possible to compare the original data with the processed data. An unambiguous participant identification code will be used to allow identification of all the data reported for each participant.

## **9.3 Access to Data**

Direct access will be granted to authorised representatives from the Funder, host institution and the regulatory authorities to permit project-related monitoring, audits and inspections - in line with participant consent.

9.4 Archiving

Disposal date of personal data is six months from project start and three years from project start date for remaining data. As there will not be no hard-copy data no archiving is needed.

**10. TRIAL OVERSIGHT**

**10.1 Role and responsibilities of the Sponsor**

WMAHSN is the sponsor for this project and will undertake the responsibilities of sponsor as defined by the Research Governance Framework and ICH GCP. An authorised representative of the Sponsor has approved the final version of this protocol with respect to the project design, conduct, data analysis and interpretation.

**10.2 Role and responsibilities of the Funder**

Funding for this trial is provided by WMAHSN. The design and management of this project are entirely independent of the funder and are performed by CU lead researchers.

**10.3 TRIAL MANAGEMENT ARRANGEMENTS**

The project lead will have responsibility for overseeing day to day coordination of the project and reporting regularly to the project lead. The project lead responsibilities include, but are not limited to:

- Coordinating protocol development, participant and project management documents
- Correspondence with project funder and tracking of progress against agreed key performance indicators
- Ensuring necessary approvals are in place before project start;
- Providing data management support; including data input, maintenance of the project database and raising of queries
- Producing in-between progress reports and coordinating internal/external meetings and minutes;
- Ensuring data security and quality and ensuring data protection laws are adhered to;
- Ensuring complete records are in place for audit and monitoring purposes;
- Ensuring the project is conducted in accordance with the ICH GCP.

### 11. MONITORING, AUDIT & INSPECTION

The project will be monitored by the Research Governance team at CU, to ensure that the project is being conducted as per protocol, adhering to Research Governance and GCP. The approach to, and extent of, monitoring has been specified in the Information Governance Unit determined by the risk assessment undertaken prior to the start of the project.

# 12. ETHICAL AND REGULATORY CONSIDERATIONS

**12.1 Ethical approval and research governance**

The project will be conducted in compliance with the principles of the ICH GCP guidelines and in accordance with all applicable regulatory guidance, including, but not limited to, the UK policy framework for health and social care research. Ethical approval for this project will be sought from the CU Research Ethics Committee. No project activities will commence until favourable ethical opinion has been obtained. The final report at the conclusion of the project will be submitted to the approving CU Research Ethics Committee.

**12.2 Peer review**

The current project has not undergone independent peer review but has been reviewed by CU Research Ethics Committee as well as partners from platform developer, Diabetes UK and WMAHSN.

**12.3 Public and Patient Involvement**

Within the context of the current project no public and patient involvement activities will be performed to decide upon project aim, design etc.

**12.4 Data protection and patient confidentiality**

The project will comply with the GDPR and regular checks and monitoring will be undertaken by the project lead to ensure compliance. Participants have been and will be assigned a unique identifier upon enrolment in to the project to allow link-anonymisation of participant-identifiable data. Access to patient identifiable data will be restricted to members of the project team who require it for the performance of their role. A GDPR acknowledged and approved transcribing service (called Just Delegate) will be used to type out case study interviews and online semi-structured interviews in verbatim. Electronic data (i.e. survey results) will be stored on shared OneDrive folder and hard copies of project documents will be stored in locked filing cabinets in secure entry-card protected sites at CU.

**13. DISSEMINATION POLICY**

Data resulting from the current project are owned by WMAHSN but the funder grants CU licence to use materials for academic research, teaching and education purposes. An intermediate and final project report will be written by the involved project team members of CU. Participants will receive a short anonymised summary report of the main findings. This will be lay people friendly and contains non-commercially sensitive findings. In case an anonymized case study will be published, this will need to be agreed upon by all project partners.

**18. Attachment_4: First Survey**

*Please complete as much information as possible about yourself (or the one you are taking care of) in the survey below.* *All information will be treated in confidence and nothing will be linked to you.*

**Sociodemographic background**

1. What is your current age?

_________________________years old

1. What is your gender?

□ Female

□ Male

□ Other, please describe

□ Prefer not to say

1. What is your ethnicity?

□ White

□ English/Welsh/Scottish/Northern Irish/British

□ Irish

□ Gypsy or Irish Traveller

□ Any other white background, please describe ________________

□ Mixed/Multiple ethnic groups

□ White and Black Caribbean

□ White and Black African

□ White and Asian

□ Any other Mixed/Multiple ethnic background, please describe ___________

□ Asian/Asian British

□ Indian

□ Pakistani

□ Bangladeshi

□ Chinese

□ Any other Asian background, please describe ____________

□ Black/African Caribbean/Black British

□ African

□ Caribbean

□ Any other Black/African/Caribbean background, please describe

□ Other ethnic group

□ Arab

□ Any other ethnic group, please describe

□ Any other ethnic group, please describe _________________________

□ Prefer not to say

1. What is your religion?

□ No religion

□ Christian

□ Buddhist

□ Hindu

□ Jewish

□ Muslim

□ Sikh

□ Any other religion (please state_______________________________________)

□ Prefer not to say

1. What is your relationship to Diabetes?

□ Type 1 diabetes

□ Type 2 diabetes

□ Gestational diabetes

□ I have a relative with Type 1 diabetes

□ I have a relative with Type 2 diabetes

□ Other type of diabetes, please describe _________________________

□ Prefer not to say

1. What is your current employment status? (if other please specify)

□ Full-time

□ Part-time

□ Student

□ Unemployed

□ Unable to work

□ Other, please specify_________________________

□ Prefer not to say

1. What is your education level?

□ High/Secondary school

□ College

□ University - Undergraduate

□ University - Postgraduate

□ Other, please specify_________________________

□ Prefer not to say

1. What is your marital status?

□ Never married or never registered in a civil partnership

□ Married or in a civil partnership

□ Divorced

□ Separated

□ Widowed

□ Cohabiting

□ Single

□ Prefer not to say

1. How many people are currently in your household?

□ 1

□ 2

□ 3

□ 4

□ 4+

□ Prefer not to say

1. Where do you live?

□ England

□ Northern Ireland

□ Scotland

□ Wales

□ Other (please specify)

□ Prefer not to say

1. Do you have any long-standing illness, disability or infirmity? By long-standing I mean anything that has troubled you over a period of time or that is likely to affect you over a period of time?

□ No

□ Yes

□ Prefer not to say

If yes, does this illness/illnesses or disability/disabilities limit your daily activities in any way?

□ No

□ Yes

□ Prefer not to say

**Device Usage**

1. On what device do you use the platform?

□ On an Android smartphone/tablet

□ On an Apple iPhone/iPad

□ On a computer with internet

2. Do you have mobile internet and/or wifi on your computer/smartphone/tablet?

□ Yes, I have mobile internet

□ Yes, I have wifi connection

□ Yes, I have mobile internet and wifi connection

□ No, I have none of them

3. For what purpose do you use your computer/smartphone/tablet the most?

□ Social media (like facebook, twitter, instagram)

□ Call/text/whatsapp

□ Listen to music (like Spotify, Youtube)

□ Search for information (like Google)

□ Other, please specify_________________________

4. Do you use your computer/smartphone/tablet to monitor and/or improve physical activity?

□ No

□ Yes, please specify_________________________

5. Do you use your computer/smartphone/tablet to monitor and/or improve your nutrition?

□ No

□ Yes, please specify_________________________

6. Do you use your computer/smartphone/tablet to monitor and/or improve your blood glucose level?

□ No

□ Yes, please specify_________________________

**Computer Proficiency Questionnaire – 12 (CPQ-12)**

This questionnaire asks about your ability to perform a number of tasks with a computer. Please answer each question by placing an X in the box that is most appropriate. If you have not tried to perform a task or do not know what it is, please mark “NEVER TRIED”, regardless of whether or not you think you may be able to perform the task.

**Computer/Smartphone/Tablet Basics**

| I can | Never tried_1_ | Not at all_2_ | Not very easily_3_ | Somewhat easily_4_ | Very easily_5_ |
| --- | --- | --- | --- | --- | --- |
| Use a computer/smartphone/tablet keyboard to type |  |  |  |  |  |
| Use a mouse or navigate on a smartphone/tablet |  |  |  |  |  |

**Printer**

| I can | Never tried_1_ | Not at all_2_ | Not very easily_3_ | Somewhat easily_4_ | Very easily_5_ |
| --- | --- | --- | --- | --- | --- |
| Load ink into the printer |  |  |  |  |  |
| Fix the printer when paper jams |  |  |  |  |  |

